### **Corresponding author:**

[name], Clinical Senior Lecturer, Institute of Applied Health Research, College of Medical and Dental Sciences, University of Birmingham, [name]

[[contact]](mailto:[contact]), (registered on BMJ site as [contact])

[contact]; [contact]

**Summary of 2-year follow-up protocol:** The Gambia has high rates of under-5 death from diarrhoea and pneumonia that peak during the weaning age. Community-based interventions may reduce weaning-food contamination and disease rates. A clustered randomised controlled trial was conducted in the Central River Region of the Gambia in 2012-15 to trial a community level weaning-food safety and hygiene intervention.

The initial registered protocol outlined a 6-month follow-up. A random sample of 30 villages (clusters) with a population of 200–450 was selected and after a baseline survey clusters were randomly assigned using a random number table within strata 1:1 to either – four intensive days of a community level campaign like intervention to improve weaning-food hygiene practices plus a reminder visit at 5 months, delivered through traditional Gambian performing arts and the existing public health and village structures – or to a one day community intervention campaign for use of water in domestic gardening in the control arm. The primary outcome was a composite score of five key food-related hygiene behaviours (observed), hereafter called 5-behaviours. Secondary outcomes included microbiological contamination of food and water for child's consumption; the prevalence of diarrhoea and respiratory diseases; and mothers' reporting of diarrhoea admission. Outcomes were measured at 6 months after the intervention in a cross-sectional survey of 20 randomly selected mothers with a child aged 6–24 months per village. Outcomes were compared in an intention-to-treat analysis between intervention and control group adjusted for mother's age, mother's education, sex of the index child, and number of children in the household.

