## **1. Protocol for 6-month follow-up of communities in the cRCT investigating the effect of weaning-food hygiene community intervention in rural Gambia.**

### **1.1 Background**

Two small proof of concept individually randomised efficacy trials (in Mali and Bangladesh) used Hazard Analysis and Critical Control Points (HACCP) to identify critical control points for improving weaning-food hygiene and related mother’s behaviour inculcated in a programme of individual training and follow-up of mothers. A recent community intervention conducted in Nepal successfully tested such interventions as part of a community mobilisation intervention using the motivational behaviour change model (based upon research in psychology that proposes ways of classifying various drivers of human behaviour) in a before-and-after cluster study. The former study was too intensive to

be scalable, while the latter needs to be evaluated in a larger trial and further simplified for scaling up in size.

We describe here the design of a complex public health community intervention for our cluster-randomised control trial (cRCT). The primary objective of the trial was to investigate the effects of the complex public health community intervention that sought to improve mothers' weaning-food hygiene practices, and further to investigate the effect of the intervention on the level of microbiological contamination in food and water ready for child's consumption, the prevalence of diarrhoea and respiratory symptoms, and diarrhoea admission, as reported by the mothers.

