#### **1.2.11 Analysis of evaluation data**

The outcome analysis will be by intention-to-treat, however, missing data will be reported and associations between outcomes explored. Mixed models will be used to adjust for clustering. The outcomes are either binary (e.g. diarrhoea in the last seven days), continuous (e.g. the total coliform counts), or count (5-behaviours). The primary outcome (5-behaviours) will be analysed using a mixed effect Poisson regression model, with the number of completed behaviours as the outcome, and an offset for the number of opportunities to exhibit the behaviour. For all secondary outcomes, we will use a mixed effect linear regression model for continuous outcomes, and a Poisson mixed effect model with a log link for binary outcomes. All models will contain robust standard errors to allow for the misspecification of the variance. Data will be transformed, where necessary, if the transformation will improve the model. We will consider the comparisons to be significant at the 5% level (report 95% CIs).

For all outcomes, the primary analysis will be unadjusted for all covariates other than cluster and those covariates used in the stratified randomisation procedure (i.e. north / south of river

and village size). The secondary analysis will also adjust for a set of pre-specified and clinically important covariates (age and education of mother, parity, sex of child, order of intervention implementation, and other intermediate outcomes where health outcomes are concerned).

Where available, baseline data will be inserted as a co-variate in the analysis. All analyses will be conducted using Stata 15.

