### **2.1.5 Statistical analysis for 2 years evaluation data (including additional variables in 2.1.1 and 2.1.2)**

The statistical analysis plan for the analysis of the 2-year follow-up evaluation data will follow the same analysis plan described earlier for the 6-month follow-up evaluation data.

Sub-group analysis will be performed to establish the effect on the ‘new mothers’.

All analyses will be conducted using Stata 15.

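### The secondary adjusted analysis of the health outcomes conditions on post-randomisation intermediate outcomes, so its arm coefficient is not the intention-to-treat effect; the primary analysis is unaffected.

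*Protocol*

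**What the plan says.** Protocol section 1.2.11 declares its principle first: "The outcome analysis will be by intention-to-treat". It then sets two tiers of analysis.

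- **Primary:** "For all outcomes, the primary analysis will be unadjusted for all covariates other than cluster" and the stratification factors (side of the river and village size).
- **Secondary:** "The secondary analysis will also adjust for a set of pre-specified and clinically important covariates". These are mother's age and education, parity and child's sex, and the list ends with "order of intervention implementation, and other intermediate outcomes where health outcomes are concerned".

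The intermediate outcomes are not named. No mediation or direct-effect aim is attached to the model that contains them. The same section applies one reporting rule to the comparisons: "We will consider the comparisons to be significant at the 5% level (report 95% CIs").

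Section 2.1.5 says that the 2-year plan "will follow the same analysis plan described earlier for the 6-month follow-up evaluation data". Its title extends this to the variables added in 2.1.1 and 2.1.2, so the clause also reaches ARI hospitalisation and the mother's own diarrhoea.

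The opening summary gives a different adjustment set for the 6-month comparison: mother's age, mother's education, "sex of the index child, and number of children in the household". It contains no intermediate outcome.

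**The concern.** A covariate in a randomised comparison should be something that the intervention cannot change. The protocol describes a chain: the campaign changes hygiene practices, which lower contamination, which lowers illness. Section 1.1 sets out first to measure the effect on practices and "further to investigate the effect of the intervention on the level of microbiological contamination in food and water", and then the effect on illness. Variables that are intermediate to a health outcome are links in that chain.

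Once they are in the model, the arm coefficient compares villages as if behaviour and contamination were the same in both arms. That is a different question from whether the programme reduced illness. It also loses the protection of randomisation, because mothers with equal behaviour scores in the two arms need not be alike in other respects.

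At stake is the reading of the adjusted health results. They would sit beside the primary estimates as if they were a refinement, and could look null or adverse for a programme that works.

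**Working it through.** **Figure to reproduce.** The protocol states no number that depends on this covariate choice, so the size below is an illustration.

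**Which variables are meant.** Section 1.2.5 lists behaviours, coliform growth, illness and admission. Of these, only behaviours and coliform growth precede illness on the protocol's chain. That is an inference, though a strong one. Under 1.2.3 to 1.2.5 both are recorded on the single evaluation day, whereas illness covers the previous seven days and admission refers to the last episode. The supposed intermediate is therefore recorded after the illness it is meant to explain.

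**Inputs from the protocol**

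- Correct behaviour in controls: 17/150 = 11.3% (1.2.6).
- Increase in behaviour: 25 percentage points, to 36.3% (1.2.6).
- Control diarrhoea risk: 26.5% (1.2.1). This is a regional two-week figure for under-5s, used as a stand-in for the 7-day risk.
- Total effect: RR 0.70, from the 30% ARI reduction at 6 months (2.1.1.2), used as a stand-in.

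**Algebra.** Use the protocol's log-link model with arm A and behaviour proportion M: ln(risk) = a + d·A + b·M. The total effect is approximately ln RR = d + b × 0.25 = ln 0.70 = −0.357. Adjusting for M leaves only d. If a share s of the log effect runs through M, the adjusted RR is 0.70^(1−s):

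- s = 0: 0.70
- s = 0.5: d = −0.357/2 = −0.178, so RR = exp(−0.178) = 0.84
- s = 1: d = 0 and b = −0.357/0.25 = −1.43, so RR = 1.00

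**Simulation.** 30 villages × 20 mothers, 300 runs per scenario, with an assumed 10 behaviour opportunities per mother. Poisson log-link models were fitted with and without the behaviour score. Village effects were left out of the fit, so only point estimates are compared. The common cause is a standard normal household factor. Per SD it lowers the log-odds of correct behaviour by 0.7 (moderate) or 1.2 (strong), and raises log illness risk by 0.3 or 0.5. The mediated share and these strengths are assumptions.

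| Scenario | RR without intermediate | RR with intermediate | Runs with adjusted RR > 1 |
|---|---|---|---|
| Full mediation, no common cause | 0.71 | 1.01 | 52% |
| Half mediation, no common cause | 0.69 | 0.81 | 15% |
| Full mediation, moderate common cause | 0.74 | 1.28 | 96% |
| Full mediation, strong common cause | 0.79 | 1.40 | 97% |
| Half mediation, strong common cause | 0.74 | 1.19 | 88% |

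The half-mediation value of 0.81 differs from the algebraic 0.84 by simulation error; both are about 0.8. The mean RR without the intermediate stays protective in every row (0.69 to 0.79).

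**The case against.** The strongest reply is that the protocol already protects the main estimate. Section 1.2.11 makes the analysis without these covariates primary for every outcome, and the clause applies only to health outcomes, so the 5-behaviours primary outcome is not touched. This stands and sets the scope of the point.

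A second reply is that the authors call the variables intermediate, confine them to health outcomes and say that associations between outcomes will be explored, so an explanatory purpose may be intended. This stands only in part. The exploration is a separate statement, and the clause puts the variables in one list with age, education, parity and sex, under an intention-to-treat heading.

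Third, the sizes rest on assumptions. Behaviour observed on one day is a noisy measure, so adjusting for it would block less than the full pathway. This stands: an RR of 1.0 is the extreme case, and attenuation is the general result.

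Fourth, the 6-month results were already known when section 2 was written (2.1.1.2), and the summary's adjustment list has no intermediate outcomes. The clause may never have been applied at 6 months. This also stands, and it directs the remedy to the 2-year analysis.

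A reader might infer that the plan removes or reverses the intervention effect on illness. The documents do not support that. The primary estimates are free of the problem, complete removal needs full mediation, and reversal needs a common cause of behaviour and illness that the protocol neither describes nor quantifies.

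**Conclusion.** The rule is wrong as written, but its reach is limited to the secondary adjusted analysis of the health outcomes. There the arm coefficient does not estimate the intention-to-treat effect. Its attenuation depends on how much of the effect the intermediate outcomes carry: on the stand-in inputs, from about 0.7 to about 0.8 at half mediation and 1.0 at full mediation. Values above 1 (1.19 to 1.40 in the scenarios tried) arise only under the assumed common cause.

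Two premises carry the conclusion: that the unnamed variables are the behaviours and contamination measures, and that the adjusted coefficient would be read as an intervention effect. The placement of the clause supports the second.

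This should be corrected before the 2-year analysis. It does not undermine the trial's main health estimates, because the primary analysis is valid.

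**What to change.** In section 2.1.5, state an exception to the 6-month plan: the intermediate-outcome clause of 1.2.11 does not apply to the adjusted models for the 2-year health outcomes. Leave the other covariates listed there, including order of implementation, as they are.

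Reconcile that list with the one in the opening summary. The summary has no intermediate outcomes and no implementation order, and names number of children in the household where 1.2.11 has parity.

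If the mechanism is of interest, report any model containing intermediate outcomes separately. Label it an exploratory mediation analysis, name the intermediates and state the assumptions. Any such model already fitted at 6 months should be relabelled in the same way and not presented as an adjusted intervention effect.

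The cost is a sentence in 2.1.5 and one harmonised covariate list. No new data are needed, and the primary analysis does not change.

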#### **1.2.12 Deviation from original analysis plan**

Rather than using logistic models, a Poisson model will be used for the (primary) count outcome, and a Poisson model with a log link for the (secondary) binary outcomes. This allows the results to be presented as an incidence rate ratio and as a relative risk, rather than an odds ratio – which will allow the results to be more easily interpreted.

#### **1.2.13 Health economic analysis**

If the intervention is effective in reducing the presence of infant diarrhoea and respiratory diseases, there are likely to be important economic implications. The economic analysis will compare the costs and outcomes associated with the community-based programme to promote hygienic weaning-food handling practices, with the control. The primary base case analysis will adopt a societal perspective; this is important for the Gambia as out-of-pocket expenditure on healthcare is high. Resource use data was collected prospectively in the trial, to estimate the costs associated with the promotion programme compared with the control.

This included out-of-pocket costs, healthcare costs and the costs of the intervention.

Information on unit costs or prices will be sourced to attach to each resource use item, to generate individual level cost estimates. The main economic analysis will assess cost-effectiveness based on cost per disability-adjusted life year (DALY) averted, used widely in the literature, with a secondary analysis of cost per case of diarrhoea avoided, and cost per

death due to diarrhoea averted. A decision analytic model will be used to assess the cost-effectiveness of the intervention beyond the end point of the trial. We will use a range of cost-effectiveness thresholds, as recommended by WHO. The estimates of DALY losses associated with childhood diarrhoea will be drawn from the existing.

**Table 1.** Showing critical control points and corrective measures prioritised for the Gambia formative research. These became the target practices for the hygiene promotion campaign: five weaning-food hygiene and one infant drinking water hygiene practices.

| Critical Control Points    | Corrective Measures – Behaviours the intervention aimed to improve                                  |
|-----------------------------------|------------------------------------------------------------------------------------------------------------|
| Before food preparation           | Hand washing with water and soap before food preparation.                                           |
|                                   | Washing of pots and utensils before food preparation and drying on a clean (and cleanable) surface. |
| Cooking                           | Hand-washing with clean water and soap when contaminated during cooking.                            |
| Food storage                      | Reheating of pre-made food after storage before feeding.                                            |
| Feeding practice                  | Hand-washing with clean water and soap before feeding child (mother) or eating (child).             |
| Water ready for drinking by child | Boiling of water ready for drinking of child.                                                       |

**Table 2.** Summary of intervention activities during visits to intervention villages/cluster.

| Day of village visit | Activities                                                                                                                                                                                                                                                                                                                                                                                                                                                   |
|----------------------|--------------------------------------------------------------------------------------------------------------------------------------------------------------------------------------------------------------------------------------------------------------------------------------------------------------------------------------------------------------------------------------------------------------------------------------------------------------|
| 1                    | Meeting Alkalo (village head).
Village Announcements about the presence of team and evening meeting.                                                                                                                                                                                                                                                                                                                                                      |
|                      | House-to-house visit with health volunteers and TBAs & village level drum/sing the 6 messages & invitation to pm meeting.                                                                                                                                                                                                                                                                                                                                    |
|                      | Afternoon event at a central point for all villagers: Through drama, videos and quizzes to impart the primary purpose and the 6 messages; obtain pledges from mothers to commit to practice the promoted behaviours and aim to become MaaChampion .                                                                                                                                                                                     |
|                      | New community volunteers ( MaaSupervisors ) training to encourage and visit/supervise mothers of <5yr children.                                                                                                                                                                                                                                                                                                                                       |
| 2                    | Meeting Alkalo & announce to villagers the presence of the team.                                                                                                                                                                                                                                                                                                                                                                                             |
|                      | House-to-house visit with MaaSupervisors to check on mother's understanding & adherence to practices; promotion of mothers to MaaFambo or MaaChampions .                                                                                                                                                                                                                                                                  |
|                      | Ad-hoc women or men meeting held separately in neighbourhoods to reinforce messages through stories and demonstrations.                                                                                                                                                                                                                                                                                                                        |
| 3                    | As in day 2 plus an afternoon event similar to day 1.                                                                                                                                                                                                                                                                                                                                                                                          |
| 4                    | As in day 3.
Additionally in the afternoon event take Group pictures with all MaaChampions , MaaSawarr and MaaFamboos for the honour board.
During a village-wide ceremony , erect a weaning-food hygiene board at village entrance with drumming/campaign songs & present certificate to the Alkalo; offer villages motivational advice on sustainability by Alkalo, MaaSupervisors and PHOs. |
| 5                    | As in day 3. Plus motivate community volunteers and MaaChampions to continue their work beyond the project team visits.                                                                                                                                                                                                                                                                                                                               |

## **2. Protocol for the second evaluation of clusters at 2-year follow-up investigating the effect of weaning-food hygiene community intervention in rural Gambia**

### **Introduction**

The objective is to ascertain any residual effect from the intervention for all the outcome measures at 30-months follow-up since the 4 days campaign activities and 2-year follow-up since the reminder 5th-month visit was carried out. (Intervention was village visits on days 1,2,17,25 and volunteer home visits in between, constituting the main intervention hereafter called the 4-day village campaign visits, plus a reminder visit at the 5th-month after these initial 25 days).

For the main cRCT outcome measures, the procedure for evaluation at 6-months will be repeated by a new recruit of 26 female data collectors who will be trained as with the previous group of data collectors at 6month. The same tools will be used with minor changes for 2 years as appropriate. However, some additional secondary research questions and sub-studies with respect to the index child and adults have been added as described below. Two nested studies took place at the same time also which helped to mask the data collection for the trial outcomes.

